## Qualitative Data

A *guided semi-structured interview* (Reinders, 2015) was developed with respect to aspects of the MRC framework (e.g., acceptability, fidelity/delivery), empirical considerations prior to the intervention and questions that arose over the course of the intervention (e.g., in conversations with exercise therapists). During the interviews, we ask exercise therapists about their experiences with patients in the ImPuls groups they conducted, their opinions about the program content regarding motivational and volitional BCTs and exercise, the perceived applicability of the program (regarding target group, general conditions in the outpatient rehabilitative and medical care facilities, ImPuls smartphone application and their own qualification) and their opinion on a possible long-term implementation of the ImPuls intervention. Possible reports of specific difficulties in implementing the program can provide us with information on why they may have had to deviate from the manual (adherence). Additionally, it can inform us regarding the areas in which they should have received more training. In summary, the interview focuses on facilitators and barriers for the implementation of the ImPuls intervention from exercise therapists’ perspectives. Interviews are conducted face to face by researchers of the process evaluation team with 20 exercise therapists, who all conducted at least one ImPuls group. The interviews have an estimated average duration of 50 minutes.

A *focus group interview* was developed analogous to the procedure mentioned above. It is supposed to provide an in-depth insight into managers’ perspectives concerning the perceived barriers and facilitators regarding the feasibility of the ImPuls intervention in the outpatient setting and its possible long-term implementation in the future. The focus group interview is conducted with 10 managers and is estimated to last 120 minutes.

Face to face interviews as well as the focus group interview are conducted once there are no further ImPuls groups in the respective outpatient rehabilitative and medical care facility. All interviews will be audio-recorded. Subsequently, the audio-records are saved on a secured network drive of the University of Tübingen and transcribed verbatim by research assistants. All mentions of personal data are masked during the transcription.

To assess *fidelity*, we record all 10 inhouse sessions of each ImPuls group conducted by the exercise therapists (except outdoor running activity) on video. We will then randomly select one video for each group out of the eight core sessions to evaluate. This corresponds to 12,5% of all core sessions and 10% of all recorded sessions. Randomization is done by an independent person who creates a randomization list using the software R version 4.1.2 (R Core, 2021). We will develop separate rating forms for each ImPuls session. Research assistants of the evaluation team will rate the sessions with regard to adherence to the treatment manual and quality of delivery. Raters will be trained in understanding the ImPuls manual and central features (setting S.M.A.R.T. goals, implement coping plans, execution of 30 minutes of exercise, discussion about perceived exertion, planning of preferred individual exercise training plans). Adherence to the treatment manual is assessed by rating with “yes” (presence) or “no” (absence) as to whether pre-defined core elements of the ImPuls intervention are delivered. An overall inter-rater reliability score is calculated. Adherence is calculated according to the overall amount of “yes”/”no” answers of these items. Subsequently, the percentage of all items answered with “yes” is calculated in order to determine the final adherence percentage score. Quality of delivery is rated once per session on a 4-point Likert scale ([1] totally agree – [4] totally disagree) using four items (exercise therapist listens actively, allows breaks and periods of reflection to take place [tolerates silence], includes all participants, takes statements of participants seriously). A sum score is calculated.

## Participant Timeline

*Item 13: Time schedule of enrolment, interventions (including any run-ins and washouts), assessments, and visits for participants. A schematic diagram is highly recommended.*

**Figure 2:** Patient Flow of the pragmatic randomized controlled trial in accordance with CONSORT

Process evaluation assessment

[figure not shown]

**Figure 3:** Design of the research project including all measurement time points of the process evaluation.

Note (Figure2): follow-up = 12 months after intervention start; Inter-1 = supervised ImPuls phase (week 1-4); inter-2 = partially supervised ImPuls phase 1 (week 5-12); inter-3 = partially supervised ImPuls phase 2 (week 13-24); post = end of the intervention (week 24); post-d = end of study period in the outpatient facility; pre = prior to intervention start in the outpatient facility; prep-1 = following the first training; prep-2 = following the second training; rando = after randomization, prior to intervention start in the outpatient facility.
TAU (=Treatment as usual) is assessed only at pre, post, and follow-up. Assessments during inter 1 (week 1 – 4), inter 2 (week 5 – 12) and inter 3 (week 13 – 24) concern only exercise therapists and patients. Assessment frequency within inter-assessments punctually differs between participants (see tables 1 – 4).

**Table 2:** Measurements for exercise therapists at each time point (following SPIRIT template).

| ASSESSMENT EXERCISE THERAPISTS | TIMEPOINT | | | | | | | | |
| --- | --- | --- | --- | --- | --- | --- | --- | --- | --- |
|  | prep-1 | prep-2 | pre | inter-1 | inter-2 | inter-3 | post | follow-up | post-d |
| Implementation |  | | | | | | | | |
| Training – satisfaction (Göhner et al., 2018) [modified] | x | x |  |  |  |  |  |  |  |
| Training – perceived skill acquisition / self-efficacy (ImPuls intervention) (Resnick & Jenkins, 2000; Rigotti et al., 2008; Rodgers et al., 2008) [adapted to Impuls] | x | x |  |  |  |  |  |  |  |
| Supervision - participation rate |  |  |  | x |  |  | x |  | x |
| Supervision – satisfaction (Göhner et al., 2018) [modified] |  |  |  | x |  |  | x |  | x |
| App - user frequency (App) |  |  |  | x | x | x |  |  |  |
| Adherence (video) |  |  |  | x |  |  |  |  |  |
| Quality of delivery (video) |  |  |  | x |  |  |  |  |  |
| Dosage - amount sessions delivered (documentation) |  |  |  | x | x | x |  |  |  |
| Mechanisms of impact |  | | | | | | | | |
| Global self-efficacy ImPuls (Rigotti et al., 2008) [adapted to Impuls] |  |  | x |  |  |  |  |  | x |
| Attitudes towards mental disorders (OMS-HC; Modgill et al., 2014) [translated + modified] |  |  | x |  |  |  |  |  | x |
| Attitudes towards manualized interventions (EBPAS-36D; Szota et al., 2021) |  |  | x |  |  |  |  |  |  |
| Motivation (SESSW; Steinmayr & Spinath, 2010) [modified]; (self-developed items) |  |  | x | x |  |  |  |  | x |
| Expectation of program success (PATHEV; Schulte, 2005) |  |  | x |  |  |  |  |  |  |
| Program acceptance/satisfaction (B&F-A; Harmsen et al., 2005) [translated + modified] |  |  | x |  |  |  |  |  | x |
| Perceived barriers (B&F-A; Harmsen et al., 2005) [translated + modified] |  |  |  | x | x |  | x |  |  |
| Satisfaction with the ImPuls group (Göhner et al., 2018, WAI-SR; Wilmers et al., 2008) [modified] |  |  |  | x |  |  | x |  |  |
| Coping strategies (DPCCQ; Orlinsky et al., 1999) [modified] |  |  |  | x |  |  | x |  |  |
| App-usability (SUS; Liang et al., 2018) [translated + modified] |  |  |  | x | x |  | x |  |  |
| App-functionality (MARS-G;Messner et al., 2020) |  |  |  |  |  |  | x |  |  |
| App-viability (self-developed) |  |  |  |  |  |  | x |  |  |
| App-satisfaction (MARS-G;Messner et al., 2020) |  |  |  | x | x |  | x |  |  |
| Context |  | | | | | | | | |
| Demographics | x |  |  |  |  |  |  |  |  |
| Qualification (self-developed) | x |  |  |  |  |  |  |  |  |
| Therapeutic experience (regarding exercise in group setting /with patients with mental disorders) (self-developed) | x |  |  |  |  |  |  |  |  |
| *Note:* follow-up = once after 12 months; Inter-1 = once at the end of the supervised ImPuls phase (week 1-4); inter-2 = once at the end of the partially supervised ImPuls phase 1 (week 5-12); inter-3 = once at the end of the partially supervised ImPuls phase 2 (week 13-24); post = after completion of the intervention (week 24-26, supervised and partially supervised) ImPuls phases; post-d = end of study period in the outpatient facility; pre = prior to intervention start in the outpatient facility; prep-1 = following the first training; prep-2 = following the second training; rando = after randomization, prior to intervention start in the outpatient facility.  *Abbreviations:* B & F – A= Barriers and facilitators assessment instrument; DPCCQ = Development of Psychotherapist Common Core questionnaire; EBPAS -36D = Evidence based practice attitude scale (German version); FPTM-40= Therapy motivation questionnaire; MARS-G = Mobile App Rating Scale (German version); OMS-HC = Opening minds scale for Health Care Providers; PATHEV = Measurement of therapy expectation and therapy evaluation of patients; SESSW = Scale for recording subjective school values; SUS = System usability scale; WAI-SR = Working Alliance Inventory – short revised (German version). | | | | | | | | | |

**Table 3:** Measurements for managers at each time point (following SPIRIT template)

| ASSESSMENT MANAGERS | TIMEPOINT | | | | | | | | |
| --- | --- | --- | --- | --- | --- | --- | --- | --- | --- |
|  | prep-1 | prep-2 | pre | inter-1 | inter-2 | inter-3 | post | follow-up | post-d |
| Context |  | | | | | | | | |
| Qualification (self-developed) |  |  | x |  |  |  |  |  |  |
| Structural characteristics of outpatient facilities (Deutsche Rentenversicherung Bund (DRV), 2014; Geidl et al., 2018; GKV Spitzenverband) [modified] |  |  | x |  |  |  |  |  |  |
| Motivation (self-developed) |  |  | x |  |  |  | x |  | x |
| Satisfaction (Göhner et al., 2018; Johnson & Caldwell, 2011) [modified] |  |  |  |  |  |  | x |  | x |
| Perceived barriers (B&F-A; Harmsen et al., 2005) [translated + modified] |  |  | x |  |  |  | x |  | x |
| *Note:* follow-up = once after 12 months; Inter-1 = once at the end of the supervised ImPuls phase (week 1-4); inter-2 = once at the end of the partially supervised ImPuls phase 1 (week 5-12); inter-3 = once at the end of the partially supervised ImPuls phase 2 (week 13-24); Post = after completion of three ImPuls intervention groups in the outpatient facility; post-d = end of study period in the outpatient facility; pre = prior to intervention start in the outpatient facility; prep-1 = following the first training; prep-2 = following the second training; rando = after randomization, prior to intervention start in the outpatient facility.  *Abbreviations:* B & F – A= Barriers and facilitators assessment instrument | | | | | | | | | |

**Table 4:** Measurements for referring health care professionals at each time point (following SPIRIT template)

| ASSESSMENT REFERRERS | TIMEPOINT | | | | | | | | |
| --- | --- | --- | --- | --- | --- | --- | --- | --- | --- |
|  | prep-1 | prep-2 | pre | inter-1 | inter-2 | inter-3 | post | follow-up | post-d |
| Implementation |  | | | | | | | | |
| Professional background (self-developed) |  |  |  |  |  |  |  |  | x |
| Opinion on the new treatment option (Kien et al., 2021); (self-developed items) |  |  |  |  |  |  |  |  | x |
| Physical activity level (EHIS-PAQ; Finger et al., 2015) [modified] |  |  |  |  |  |  |  |  | x |
| *Note:* follow-up = once after 12 months; Inter-1 = once at the end of the supervised ImPuls phase (week 1-4); inter-2 = once at the end of the partially supervised ImPuls phase 1 (week 5-12); inter-3 = once at the end of the partially supervised ImPuls phase 2 (week 13-24); post = after completion of the intervention (week 24-26, supervised and partially supervised) ImPuls phases post-d = after end of study period in all outpatient facilities; pre = prior to intervention start in the outpatient facility; prep-1 = following the first training; prep-2 = following the second training; rando = after randomization, prior to intervention start in the outpatient facility.  *Abbreviations:* EHIS-PAQ= European Health Interview Survey - Physical Activity Questionnaire | | | | | | | | | |

**Table 5:** Measurements for patients at each time point (following SPIRIT template)

| ASSESSMENT PATIENTS | TIMEPOINT | | | | | | | | | |
| --- | --- | --- | --- | --- | --- | --- | --- | --- | --- | --- |
|  | prep-1 | prep-2 | pre | rando | inter-1 | inter-2 | inter-3 | post | follow-up | post-d |
| Implementation |  |  |  |  |  |  |  |  |  |  |
| demographics |  |  | x |  |  |  |  |  |  |  |
| Mechanisms of impact |  | | | | | | | | | |
| *Responses and interactions^1^* |  |  |  |  |  |  |  |  |  |  |
| Motivation (FPTM-40; Schulz et al., 1995) [modified] |  |  |  | x |  |  |  |  |  |  |
| Expectation of program success (PATHEV; Schulte, 2005) [modified] |  |  |  | x | x | x | x |  |  |  |
| Satisfaction with the program (SSTS-R; Oei & Green, 2008) [translated + adapted to Impuls] |  |  |  |  | x | x | x |  |  |  |
| Therapeutic alliance (WAI-SR; Wilmers et al., 2008) |  |  |  |  | x | x | x |  |  |  |
| App |  |  |  |  |  |  |  |  |  |  |
| User frequency (App) |  |  |  |  |  |  |  |  |  |  |
| Usability (SUS; Liang et al., 2018) [translated + modified] |  |  |  |  | x | x | x |  |  |  |
| Functionality (MARS-G; Messner et al., 2020) |  |  |  |  |  |  | x |  |  |  |
| Viability (self-developed) |  |  |  |  |  |  | x |  |  |  |
| Satisfaction (MARS-G; Messner et al., 2020) |  |  |  |  | x | x | x |  |  |  |
| Attendance rate (documentation) |  |  |  |  | x |  |  |  |  |  |
| Treatment dropouts (documentation) |  |  |  |  | x | x | x |  |  |  |
| *Mechanisms of change* |  |  |  |  |  |  |  |  |  |  |
| Emotional intelligence (TEIQue; Petrides & Furnham, 2006) |  |  | x |  |  |  |  | x | x |  |
| Emotion regulation (DERS; Gratz & Roemer, 2004) |  |  | x |  |  |  |  | x | x |  |
| Barrier management (Sniehotta et al., 2005) |  |  | x |  |  |  |  | x | x |  |
| Perceived stress (PSS; Schneider et al., 2020) |  |  | x |  |  |  |  | x | x |  |
| Physical activity-related health competence (PAHCO; Sudeck & Pfeifer, 2016) |  |  | x |  |  |  |  | x | x |  |
| Repetitive negative thinking (PTQ; Ehring et al., 2011) ^2^ |  |  | x |  | x | x | x | x | x |  |
| Affect (state/trait) (PANAS; Breyer & Bluemke, 2016)^1, 2^ |  |  | x |  | x | x | x | x | x |  |
| Affect/repetitive negative thinking during the program (App)^1, 3^ (self-developed) |  |  |  |  | x | x | x |  |  |  |
| Goal attainment during the program (App)^1, 3^ (visual analogue scale) |  |  |  |  | x | x | x |  |  |  |
| Barrier management during the program (App)^1, 3^ (visual analogue scale) |  |  |  |  | x | x | x |  |  |  |
| Frequency, intensity, time/duration and type of physical activity (FITT criteria, App)^1, 3^ |  |  |  |  | x | x | x |  |  |  |
| *Note*: follow-up = once after 12 months; Inter-1 = once at the end of the supervised ImPuls phase (week 1-4); inter-2 = once at the end of the partially supervised ImPuls phase 1 (week 5-12); inter-3 = once at the end of the partially supervised ImPuls phase 2 (week 13-24); post = after 6 months; post-d = end of study period in the outpatient facility; pre = before randomization, prior to intervention start in the outpatient facility; prep-1 = following the first training; prep-2 = following the second training; rando = after randomization, prior to intervention start in the outpatient facility ^1^ intervention group only.  ^2^ weekly assessments (inter 1 = 4 times [week 1, 2, 3 and 4]); inter 2 = 8 times [week 5, 6, 7, 8, 9, 10, 11 and 12]) / monthly assessment (inter 3 = 3 times [week 16, 20 and 24]).  ^3^ depending on patient’s usage of the smartphone application, data is collected continuously throughout the phases.  *Abbreviations:* DERS = Difficulties in Emotion Regulation Scale; FITT = Frequency, Intensity, Time/duration and Type of physical activity; FPTM-40= Therapy motivation questionnaire; MARS-G = Mobile App Rating Scale (German version); PAHCO = Physical Activity-related Health Competence questionnaire; PANAS = Positive and Negative Affect Schedule; PATHEV = Measurement of therapy expectation and therapy evaluation of patients; PSS = Perceived Stress Scale; PTQ = Perseverative Thinking Questionnaire; SSTS-R = Satisfaction with therapy and therapist scale (revised); SUS = System Usability Scale; TEIQue = Trait Emotional Intelligence Questionnaire ; WAI-SR = Working Alliance Inventory – short revised (German version). | | | | | | | | | | |

## Sample Size

*Item 14: Estimated number of participants needed to achieve study objectives and how it was determined, including clinical and statistical assumptions supporting any sample size calculations.*

The sample size was determined a priori using power analysis (G*Power, version 3.1.9.2) (Faul et al., 2009; Faul et al., 2007). Power analysis was conservatively based on the lowest symptom-related post-treatment effect of exercise (vs. TAU/waiting list) on all included clinical disorders, namely the effect size of d = -0.348 (g = - 0.347) for symptoms of post-traumatic stress disorder (Rosenbaum et al., 2015). A two-sided *t*-test, alpha level of 0.05, a test power of 80%, an equal cell population, and a dropout rate of 30% were assumed. This calculation resulted in N = 375, which is conservative enough to detect the lowest expected treatment effect at the post-treatment phase. However, we regarded this sample size as the minimum and targeted a total sample of N = 600, in order to have enough statistical power for further analysis performed in the course if the process evaluation (see Statistical Methods – Items 20 a, b and c). ~~that will be predefined and published in a separate study protocol regarding the evaluation of the entire implementation process based on the Medical Research Council framework.~~

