   3. To what extent do patients’ integration of motivational/volitional core components of the ImPuls intervention (e.g., barrier management, goal-setting, phone contacts) as well as changes in respective individual behavioral determinants (e.g., action and coping plans; physical activity-related health competencies) mediate its effect on their exercise adherence?
   4. To what extent do changes in patients' transdiagnostic psychological processes (e.g., emotional regulation, repetitive negative thinking or perceived stress) mediate the treatment effects?

*Item 8: Description of trial design including type of trial (e.g., parallel group, crossover, factorial, single group), allocation ratio, and framework (e.g., superiority, equivalence, non-inferiority, exploratory).*

The study will be led by researchers based at the University of Tuebingen in Germany, and will be conducted in 10 different study sites across Baden-Württemberg, a region in South-West Germany. The entire project will be conducted between September 2020 and February 2024. The study has been registered at the German Clinical Trial Register (ID: DRKS00024152, 05/02/2021) and has been approved by the local ethics committee for medical research at the University of Tuebingen (ID: 888/2020B01, 02/11/2020). A pragmatic multi-site block-randomized controlled trial with two treatment arms (ImPuls + TAU vs. TAU) and three points of assessment (pre, post, follow-up) will be conducted (see fig. 1). All outcomes will be included at all assessments. Study completion and reporting will be carried out in accordance with the Consolidated Standards of Reporting Trials (CONSORT) [52], the Template for Intervention Description and Replication (TIDieR) (Hoffmann et al., 2016) and the Consensus on Exercise Reporting Template (CERT) (Slade et al., 2016).

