Once six patients at the same site will be found to be eligible for participation, they will receive online questionnaires via the web-based data management system REDCap (Harris et al., 2019; Harris et al., 2009) and a accelerometer-based Physical Activity sensors (MOVE 4; movisens GmbH) which will be worn for seven consecutive days (pre-assessment). Online questionnaires and the assessment of physical activity will be carried out within a period of 14 days. On Day 15, the six patients will be randomized as a group to either the intervention or control condition. In case of an assignment into the intervention condition, study sites will have to start the intervention within 14 days. Before the start of the intervention, global symptom as well as disorder-specific symptom severity will be assessed again to check whether participants meet the cut-off criteria for a mental disorder. In each study site, 60 patients are planned to be recruited and randomized, resulting in 10 allocations per site. The intervention group will complete the exercise intervention in addition to TAU, while the control group will receive TAU within the real-world outpatient mental health care setting in Germany. The TAU condition is intended to represent the typical treatment patients receive in the German outpatient health care system. The procedure of the pre-assessment phase will be repeated six months (Post) and 12 months (Follow-up) after randomization. After the completion of all assessments, patients of the control group will receive 450€ as reimbursement for their time.

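### The stated minimum of N = 375 for 80% power assumes independent patients, although the trial randomises intact groups of six; it holds only at an intracluster correlation of essentially zero

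*Protocol*

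**What the plan says.** The Sample Size section (Item 14) takes as its target effect "the effect size of d = -0.348 (g = - 0.347) for symptoms of post-traumatic stress disorder" and uses a two-sided t-test with "alpha level of 0.05, a test power of 80%, an equal cell population, and a dropout rate of 30% were assumed". Its conclusion is: "This calculation resulted in N = 375, which is conservative enough to detect the lowest expected treatment effect at the post-treatment phase". It then adds: "However, we regarded this sample size as the minimum and targeted a total sample of N = 600". The reason given for the larger number is power for the process evaluation. The section mentions no ICC, design effect or other allowance for grouping.

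The Recruitment section (Item 15) describes the allocation. Once six eligible patients at a site have completed the pre-assessment, "the six patients will be randomized as a group to either the intervention or control condition". It continues: "In each study site, 60 patients are planned to be recruited and randomized, resulting in 10 allocations per site". The trial "will be conducted in 10 different study sites across Baden-Württemberg", so the plan amounts to 10 × 10 = 100 groups and 600 patients. The Implementation section (Item 16c) agrees with this, since its permuted blocks balance the number of groups, not of patients, within each site.

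**The concern.** The power calculation and the allocation describe different designs. Patients randomised together share a site and a recruitment period, and those in the ImPuls arm also share a therapist and a training group. If their outcomes are positively correlated, the variance of the treatment difference is larger than the t-test assumes, and 375 patients carry less information than the calculation credits them with.

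What is at stake is the number declared sufficient for the primary comparison. On the protocol's own terms, a trial that ended recruitment near 375 could still be reported as having 80% power. The margin that would protect the primary outcome against clustering exists only because 600 patients are wanted for another purpose.

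**Working it through.** **Inputs from the Sample Size section.** d = 0.348 (SD = 1), two-sided alpha 0.05, power 80%, equal arms, 30% dropout. **From the Recruitment section.** Groups of six, 10 groups per site, 10 sites. **Assumed.** The ICC, because the protocol gives none; the range shown is 0.01 to 0.10.

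**Step 1: reproduce the stated figure.** With the noncentral t distribution, 130 per arm gives 79.8% power and 131 per arm gives 80.1%. So 131 per arm are needed, 262 in total, and 262 / (1 − 0.30) = 374.3, rounded up to 375. The match is exact, so no clustering allowance is hidden in the number.

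**Step 2: slack at 375.** Analysed patients: 375 × 0.7 = 262.5, or 131.25 per arm. Power at ICC 0 is 80.2%. There is almost nothing in reserve.

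**Step 3: design effect.** DE = 1 + (m − 1) × ICC. I take m = 6 (full groups) and m = 6 × 0.7 = 4.2 (mean analysed group size after dropout). Power is that of the same t-test with noncentrality d × √(n / (2 × DE)), where n is the analysed number per arm. Required total N is 262 × DE / 0.7.

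| ICC (assumed) | DE, m = 6 / 4.2 | Power at 375, m = 6 / 4.2 | N for 80%, m = 6 / 4.2 | Power at 600, m = 6 / 4.2 |
|---|---|---|---|---|
| 0.01 | 1.05 / 1.032 | 78% / 79% | 393 / 386 | 93% / 94% |
| 0.02 | 1.10 / 1.064 | 76% / 78% | 412 / 398 | 92% / 93% |
| 0.05 | 1.25 / 1.16 | 71% / 74% | 468 / 434 | 89% / 91% |
| 0.10 | 1.50 / 1.32 | 63% / 69% | 561 / 494 | 83% / 87% |

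Required N is rounded to the nearest patient, before rounding to whole groups.

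**Step 4: clustering in the ImPuls arm only.** The variance factor becomes (1 + DE) / 2. With m = 6, power at 375 is 79%, 78%, 75% and 71% at ICC 0.01, 0.02, 0.05 and 0.10. The loss is smaller but does not vanish.

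**Step 5: how much clustering 600 can absorb.** Analysed: 600 × 0.7 = 420. The largest tolerable design effect is 420 / 262 = 1.603. The break-even ICC is 0.603 / 5 = 0.12 for m = 6 and 0.603 / 3.2 = 0.19 for m = 4.2.

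**The case against.** The strongest reply is that the trial is not planned at 375. The 600 target is built into the site plan, no rule ends recruitment at 375, and no interim analysis is foreseen. This stands. A reader might infer that the trial is underpowered for its primary outcome, but Step 5 does not support that at the target size.

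A reader might also infer a calculation error. There is none: 375 is correct for the model used. The model does not match the allocation. Nor should much be made of the word conservative. The section uses it mainly for choosing the smallest effect among the included disorders, not as a claim about clustering. That 375 / 6 = 62.5 groups is only a matter of rounding.

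The size of the loss is also open to challenge:

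- Every ICC here is assumed, and at 0.01 the shortfall is only one to two points.
- Controls receive usual care without group sessions, so full clustering in both arms may be too pessimistic (Step 4).
- The protocol expects dropout below 30% and asks dropouts to continue assessments. At an assumed 20% loss, 375 gives about 82% at ICC 0.02 with m = 6.
- The planned analysis is a longitudinal multilevel model. On a change score with an assumed pre–post correlation of 0.6, 375 gives about 80% at ICC 0.05 with m = 6, taking the same ICC for the change score. At a correlation of 0.5 there is no gain.

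These points limit how far the loss can be generalised, but they do not rescue the stated figure. The Sample Size section itself assumes 30% dropout, uses a t-test and claims no gain from baseline. The Statistical Methods section names study site, not the randomised group. A separate analysis plan may treat the group in the analysis, but it would not change how 375 was derived.

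**Conclusion.** The point holds for the stated minimum. N = 375 is an independent-patient figure attached to a group-randomised design. Under the section's own inputs, 80% power is reached only at an ICC of essentially zero. With both arms clustered and 30% dropout, power is about 78–79% at ICC 0.01, falling to 63–69% at 0.10. The direction is certain for any appreciable positive ICC; the amount depends on a value the protocol does not give.

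The planned 600 retains at least 80% up to an ICC of about 0.12 (m = 6) or 0.19 (m = 4.2). It would be equally wrong to conclude that 600 suffices whatever the ICC, since it falls short above those values. Severity is moderate: a wrong stated figure and justification, not a demonstrated shortfall at the target size.

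**What to change.** In the Sample Size section (Item 14):

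1. Name the group of six as the unit of randomisation.
2. State an assumed ICC, its source and a plausible range, and whether clustering is assumed in both arms or only in the ImPuls arm.
3. Restate the minimum with the design effect, in whole groups per arm. At ICC 0.05, for example, about 434 patients (m = 4.2) or 468 (m = 6) are needed before rounding. With equal arms, 434.2 / 12 = 36.2 becomes 37 groups per arm (444 patients), and 467.9 / 12 = 38.99 becomes 39 per arm (468 patients).
4. Remove the claim that 375 suffices for the primary comparison.
5. Keep the process evaluation as the documented reason for 600, and add that this target also covers the primary comparison up to the stated ICC.

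The cost is a wording change and a short recalculation. The declared minimum rises. The recruitment target need not change unless the ICC judged plausible exceeds about 0.12 to 0.19.
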